#### Study intervention

2.2.5.

##### Treatment as usual

2.2.5.1.

All participants (experimental and control group) will continue to receive treatment as usual (TAU) at their institution. TAU may consist of psychiatric and psychosocial treatment by a multidisciplinary team, which includes mental health psychiatric nurses, psychiatrists, psychologists, social workers, occupational therapists and other mental health professionals. TAU may also include treatment in community settings, day hospital and inpatient settings, as well as antidepressant medication, psychosocial rehabilitation, socialisation groups and psychoeducational and therapeutic groups. The care of participants in TAU will not be limited or influenced in any way. To control for TAU, we will carefully record participation in concurrent treatment. The control group will not participate in the MCT-Silver programme.

##### Metacognitive training for depression (MCT-Silver)

2.2.5.2.

Metacognitive training (MCT) has its origins in 2003 with the development of “metacognitive training for psychosis” (Moritz et al., 2013, 2017). MCT has since been developed for other psychiatric disorders, e.g., depression (D-MCT; Moritz et al., 2013; Jelinek et al., 2015), and an adaptation of the D-MCT, called MCT-Silver (pilot study), has been developed for older adults with depression (Schneider et al., 2018). Although certain terms have been adapted for the Portuguese translation, case examples, exercises and general content were maintained to ensure consistency across countries. However, the intervention and examples can be tailored by the trainers to meet specific group needs of the group concerned (e.g., to reduce the length of sessions or tailor content to specific issues of group members). All information about this programme is available^2^ in English, German and Portuguese.

MCT-Silver is a manualized treatment program comprised of eight modules addressing common cognitive distortions and biases in information processing in depression as well as depression-related behaviors and metacognitive beliefs. Differing from D-MCT, MCT-Silver also includes components drawn from acceptance and commitment therapy as well as imagery rescripting. All content is supported by significant empirical work linking these processes to depression. The topics of MCT-Silver include the following: Modul 1: Mental filter; Module 2: Mood-congruent memory / false memories (Mathews and Macleod, 2005; Moritz et al., 2008); Module 3: “Should” statements (Egan et al., 2011; Mcgrath et al., 2012) and disqualifying the positive (Cane and Gotlib, 1985; Elliott et al., 1997) as well as acceptance of negative feelings (Hayes et al., 1996; Butler and Ciarrochi, 2007); Module 4: Values (Isaacowitz and Seligman, 2002; Hayes et al., 2006; Wrosch et al., 2013); Module 5: Exaggeration/Minimization (Garber and Hollon, 1980; Hoehn-Hyde et al., 1982; Cane and Gotlib, 1985; Wenzlaffand and Grozier, 1988) as well as Attribution Style (Carver and Ganellen, 1983; Wenzlaffand and Grozier, 1988); Module 6: Rumination and Withdrawal (Rood et al., 2009; Seidel et al., 2010; Wells, 2011); Module 7: Jumping to Conclusions (Strunk et al., 2006; Miranda et al., 2008), and Module 8: Self-Worth in Later Life (Davey et al., 2004; Orth et al., 2009; Holmes et al., 2016; Table 2).

**Table 2 tab2:** Descriptions of the content of MCT-Silver modules.

Module	Name	Cognitive bias/Behavior	Aims	Training example
1	Thinking and reasoning I	Mental filter, overgeneralization	Identify and modify selective perception (i.e., mental filter) and exaggerated generalizations of negative experiences.	*Modification of overgeneralization of negative experiences*: Situational examples are presented along with possible (depressive) interpretations. More helpful interpretations of these situations are identified.
2	Memory	Mood-congruent memory, false memories	Normalize and explain concentration and memory issue. Increase awareness of memory biases.	*False memory effect*: Participants are asked to remember objects presented in a picture. They are then provided with a list of words and are asked to identify the incorrect objects, which were not presented.
3	Thinking and reasoning II	“Should” statements, “all or nothing” thinking, acceptance of negative feelings related to life changes.	Encourage participants to question rigid and perfectionistic behavior Present the concept of acceptance for negative feelings.	*Examining perfectionistic standards*: The pros and cons of holding oneself to certain (high) standards (e.g., to always have a perfectly clean home) are discussed. *Acceptance*: Identification of areas in life in which participants would like to practice more acceptance.
4	Values	Identifying values and strategies for living a value-based life	Identify personal values.	Values: Communication regarding the importance of improving insight into personal values. Processing of strategies that can support a value-oriented life.
5	Thinking and reasoning III	Magnification and minimization, depressive attributional style	Identify and modify biases in judging the extent and consequences of perceived successes and failures.	*One-sided attributions*: Examples of one-sided attributions are presented, and participants are encouraged to identify multiple causes for an outcome.
6	Behaviors and strategies	Dysfunctional coping strategies: withdrawal, rumination, thought suppression	Reduce dysfunctional behaviors associated with depression. Develope new helpful coping behaviors.	*Helpful coping strategies*: Mindfulness exercise to practice gaining inner (psychological) distance.
7	Thinking and reasoning IV	Jumping to conclusions, mind reading, fortune telling (catastrophizing)	Identify instances of jumping to conclusions. Encourage consideration of multiple sources of information before reaching a conclusion.	*Considering alternative information*: Paintings are presented and participants are asked to guess the correct title from a list of choices.
8	Self-esteem	Self-esteem, changing negative self-perceptions through imagery	Communicate strategies to improve self-esteem Reduce and modify unfair comparisons (e.g., with the younger self).	Imagination exercise: Transformation of negative images into strong, positive images (e.g., transformation of a weak, nervous chick into a proud eagle).

Figure 2 shows an example of Module 7: Jumping to Conclusions.

**Figure 2 fig2:**
[figure not shown]
Example of Module 7: Jumping to Conclusions.

Through interactive exercises and a structured multimedia presentation, MCT-Silver aims to convey knowledge about cognitive distortions, helps participants to reflect critically about and change the content of their thoughts, and acquire new strategies to solve problems. Each session lasts 45–60 min (Jelinek et al., 2022).

In the current study, MCT-Silver will be applied to the experimental group by mental health and psychiatry professionals with experience in the care of individuals with depression. A training course on the application of the MCT-Silver programme will be completed by these professionals prior to the start of the study. Administration of the training will also be monitored and supervised by the study PI ([name]). For adherence monitoring of the MCT-Silver application the sessions will be recorded, and no images of the participants will be taken to safeguard ethical issues.

MCT-Silver sessions will be applied once a week for a total of eight sessions. The intervention will be applied face-to-face in groups in a quiet room of the institution to which the group belongs.

#### Data collection and outcome measures

2.2.6.

The instruments will be administered to all study participants through an interview at three planned assessments (Table 3). To characterize the sample, sociodemographic, and clinical data will be collected [age, sex, marital status, cohabitation, educational level, professional/employment status, duration of depression diagnosis (if applicable), number of psychiatric hospitalizations, medication, type of treatment, and substance use; Table 4]. These data will be collected before the start of the MCT-Silver intervention for all participants.

**Table 3 tab3:** List of study measures and questionnaires.

Instruments	Baseline	8 weeks (post)	3 months (follow-up)
Mini Mental State Examination	X		
Beck’s Depression Inventory (BDI-II)	X	X	X
Patient Health Questionnaire (PHQ-9)	X	X	X
Montgomery-Asberg Depression Rating Scale (MADRS)	X	X	X
Metacognitions Questionnaire (MCQ-30)	X	X	X
Dysfunctional Attitudes Scale (DAS-18B)	X	X	X
WHOQOL-BREF Item 1	X	X	X
Ruminative Response Scale (ERR-10-A)	X	X	X
Rosenberg Self-Esteem Scale	X	X	X
The Attitudes to Ageing Questionnaire (AAQ-12)	X	X	X
Intervention questionnaire and patient satisfaction		X	X

**Table 4 tab4:** Summary of the clinical and demographic characteristics of the sample.

Questions	Answers						
Age							
Gender	Female	Male					
Marital status	Single	Married/ marital partnership	Widowed	Divorced/separated			
Level of education	Cannot read or write	Can read and write, but has not attended school	Attended school, but not higher education	Number of years of schooling	Higher education		
Who you live with	Institution	Alone	Spouse/partner	Child	Brother/sister	Other relative	Other non-family member
Labour status	Employed	Unemployed	Retired	Retired on invalidity	On sick leave	Current or past occupation	
Do you take any medication? If yes, which one?	No	Yes	If so, which one?				
Have you ever been admitted to a psychiatric ward?	No	Yes	How many times?				
Have you ever been to a psychiatric day hospital?	No	Yes	How many times?				
Are you followed up in follow-up appointments/ programmes?	No	Yes	Which ones?				
What is your current substance consumption?	None	Tobacco	Alcohol (more than 3 drinks a day)	Other drugs, which ones?			
Do you have any diagnosed illness(es)?	No	Yes	If so, which one or ones?				

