#### Study design

2.2.1.

This study represents an observer-blind, parallel-groups randomized controlled trial.

All procedures follow CONSORT (Consolidated Standards of Reporting Trials) guidelines and follow four phases: enrollment, intervention allocation, follow-up, and data analysis. The follow-up will occur 3 months after completion of the intervention. The trial has been registered at ClinicalTrials.gov (NCT05640492).

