#### Randomization and blinding

2.2.3.

Eligible participants will be recruited at each institution (the mental health service of each hospital that agreed to take part in the study in Portugal) through telephone contact by the researchers in collaboration with the multidisciplinary team. The study will also be publicized in the media so that older adults can contact the researchers if they are interested in participating. A baseline assessment will be carried out and all instruments will be applied after informed consent from participants. All participants who agree to participate in the study will be assigned a code and will be randomly assigned to either MCT-Silver (experimental group where the intervention will be applied) or the control group (no stratification factors). This randomization will be performed using a computer program. The control group will not be administered the intervention (MCT-Silver). In both groups, treatment will be maintained as usual (Treatment As Usual – TAU) and participation in other interventions as well as use of medications will be carefully monitored. Study participants will be informed that they should not reveal which group they are in and will be reminded of this at each testing session. All participants will be re-assessed at the end of the intervention and 3 months after completion, with the application of all planned instruments. Assessments will be performed by the same rater before and after the intervention and at follow-up. Assessors will be trained in the administration of all instruments prior to the start of the study. A third researcher will inform patients of group assignment so that raters will remain blinded throughout the study. The Side Effects of Intervention questionnaire and patient satisfaction with MCT-Silver will be applied to the experimental group post-intervention (Table 1; Figure 1).

**Table 1 tab1:** Study schedule.

	Study period				
	Enrolment	Randomization	Intervention (8 weekly sessions)	Post (8 weeks)	Follow-up (3 months)
TIMEPOINT	T-1	T0		T1	T2
Enrolment:					
*Eligibility screen*	X				
*Informed consent*		X			
*Randomization*		X			
Interventions:					
*Treatment As Usual (TAU)*	X	X	X	X	X
*MCT-Silver*			X		
Assessments: *Baseline*		X			
*Post-intevention*				X	
*Follow up*					X

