### Validity and reliability/rigour

2.4.

Variables such as educational level, duration of mental disorder, and type of treatment may influence the results of this study. The proposal to use the stratified random sampling method in this study aims to minimize confounding bias. All procedures, including the implementation of the intervention will be carried out after trainers have completed MCT-Silver training to minimize the risk of bias. Participants will be randomly allocated to either the experimental group [MCT-Silver + Treatment As Usual (TAU)] or the control group (TAU only). A computer-generated stratified random sampling method will be applied taking into consideration an equitable distribution by sex and age to promote sex and age equality and inclusiveness. Finally, all raters will be blinded to participant group assignment.

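### A questionnaire meant only for the MCT-Silver arm sits among the blinded rater's interview instruments; as written this would reveal allocation at T1 and conflicts with the promise of rater blinding throughout

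*Protocol article*

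**What the plan says.** Blinding is claimed in three places of the protocol article. Section 2.2.1: "This study represents an observer-blind, parallel-groups randomized controlled trial". Section 2.2.3: "A third researcher will inform patients of group assignment so that raters will remain blinded throughout the study". Section 2.4: "all raters will be blinded to participant group assignment". Section 2.2.3 adds one safeguard on the participants' side: "Study participants will be informed that they should not reveal which group they are in", with a reminder at each testing session.

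On who assesses, section 2.2.3 states: "Assessments will be performed by the same rater before and after the intervention and at follow-up". It also says that the re-assessments at T1 and T2 use every planned instrument and that assessors are trained to administer all of them. On mode, section 2.2.6 states: "The instruments will be administered to all study participants through an interview at three planned assessments (Table 3"). The last row of Table 3 is the intervention and satisfaction questionnaire, marked at 8 weeks and at 3 months.

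On who receives that questionnaire, section 2.2.3 states: "The Side Effects of Intervention questionnaire and patient satisfaction with MCT-Silver will be applied to the experimental group post-intervention". Section 2.2.8.9 repeats this and gives sample items, which refer to the training by name. Section 2.1 places the satisfaction rating after the 8-week intervention period.

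**The concern.** A form that only one arm receives identifies the arm. If the person who gives it is also the blinded rater, that rater knows the allocation from that moment. The same rater sees the participant again at T2, so the T2 ratings would be made with that knowledge.

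Participants in this trial know whether they attended a group training, so blinding of the rater is the main protection left against biased measurement. The Discussion accepts that self-report has limited validity and says the clinician-rated MADRS was added for that reason. A MADRS rated by someone who knows the arm no longer serves that purpose well. T2 is not a minor time point: the hypotheses in section 2.1 cover both pre-post and pre-follow-up change, and section 2.2.9 plans a separate ANCOVA for each.

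**Working it through.** No arithmetic applies. The point rests on no significance level, power, effect size or dropout rate, and there is no stated figure to reproduce. The check sets the statements side by side.

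1. The questionnaire is a Table 3 instrument at T1 (section 2.2.6, Table 3).
2. Table 3 instruments are given by interview at the planned assessments (section 2.2.6).
3. The same rater performs those assessments at T0, T1 and T2; assessors are trained in all instruments, with none excepted (section 2.2.3).
4. Only MCT-Silver participants receive the questionnaire (sections 2.2.3 and 2.2.8.9).

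From 1 to 4, a rater who follows the text asks MCT-Silver participants about the training at T1 and does not ask TAU participants. Both arms are then identified for everyone seen at T1. Taking section 2.2.6 at its word and giving the form to every participant does not help, because items about a named training would still separate those who attended it from those who did not.

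Neither stated safeguard reaches this form. The third researcher's task is to tell patients their group. The instruction to participants concerns what they disclose themselves, and a planned interview about the training would work against it.

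If the rater does give the form, the exposure by outcome is:

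| Outcome | T0 | T1 | T2 |
|---|---|---|---|
| MADRS (secondary, clinician-rated) | none | only if the form comes first | exposed |
| BDI-II (primary, self-rated, by interview) | none | lesser, and only if the form comes first | lesser |

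The article does not state the order of instruments within a visit, so the T1 column cannot be settled.

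Two contradictions remain whoever gives the form. Table 3 marks it at 8 weeks and 3 months, while sections 2.1, 2.2.3 and 2.2.8.9 place it after the intervention. Section 2.2.6 says the instruments go to all participants, while sections 2.2.3 and 2.2.8.9 limit this one to the experimental group.

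**The case against.** The strongest reply is that no sentence names the rater as the person who gives this form. Sections 2.2.3 and 2.2.8.9 say only that it will be applied, without saying by whom, and in section 2.2.3 that statement directly follows the one about the third researcher. The sentence in section 2.2.6 also cannot be literal for this row: the form is not for all participants and has no baseline mark, and the MMSE is given at baseline only. The form itself looks self-completed, with first-person Likert items and open sentence stems, and the Discussion mentions reading competence as an influence on self-report. Finally, a journal article condenses, and the full protocol may assign the task elsewhere.

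Much of this stands. It shows that the link to the rater is an inference from several statements, so the point is a contradiction to resolve and not proof that blinding will fail in practice. It does not remove the point. The article does state who assesses, with which instruments, by what mode and in which arm, and those statements conflict with its own blinding claim. Self-completion would not settle who hands out and collects the form.

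A reader might go further and infer that blinding is lost for every participant, that all T2 BDI-II and MADRS values are equally compromised, and that the error favours MCT-Silver. The document does not support that. The BDI-II is rated by participants who know their arm, so rater blinding was never its chief protection. T1 exposure depends on an unstated order. Nothing in the text shows the size or direction of a bias.

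**Conclusion.** The stated assessment procedure and the stated blinding conflict. Followed as written, the procedure would show the rater each assessed participant's arm at T1. The clearest consequence is for one clinician-rated secondary outcome, the MADRS, at T2. The BDI-II is less exposed, and the T1 outcomes are exposed only if the form precedes them. The size and direction of any resulting bias cannot be derived from the document.

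This rests on reading sections 2.2.3 and 2.2.6 and Table 3 together, with no other person assigned to the form. If the full protocol assigns it to someone outside the rating team, the exposure disappears, but the disagreements over time points and recipients still need correction. The matter should be settled before T1 data are collected, because a rater who has learned the allocation cannot be blinded again.

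**What to change.** - State in sections 2.2.3 and 2.2.8.9 that the side-effects and satisfaction questionnaire is given by the third researcher, who already knows the allocation, or is self-completed and returned sealed. In either case it comes after all outcome measures at that visit.
- Keep the form and its data out of the raters' forms and data view.
- Except this form from the interview battery and from the reference to all participants in section 2.2.6, so that it agrees with sections 2.2.3 and 2.2.8.9.
- Reconcile the two time points in Table 3 with sections 2.1, 2.2.3 and 2.2.8.9. If a 3-month administration is intended, say so in the text and handle the form in the same way at T2.
- Optionally, have raters record their guess of allocation at T1 and T2. This is good practice but is not needed to remove the contradiction.

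The cost is a few sentences and a small change in assessment logistics. It uses a researcher already in the plan, so no extra staff are needed, and sample size, power and significance level are unaffected.

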##### Mini Mental State Examination (MMSE)

2.2.6.1.

The MMSE will be applied to screen for cognitive deficits. Participants with cognitive impairments according to the cut-offs for the MMSE will be excluded from the study. This instrument evaluates cognitive function and was developed by Folstein et al. (1975). It is composed of six groups of questions that assess orientation to time and place, attention / concentration, short-term memory (recall), language skills, visuospatial abilities and ability to understand and follow instructions. Higher scores indicate better cognitive ability. The MMSE was adapted for the Portuguese population (Guerreiro et al., 1994). The cut-off for establishing cognitive impairment adjusted for years of education and, thus, also exclusion from the study is as follows: 0 years education ≤15 points; 1-11 years of education ≤22 points; 11+ years of education ≤24 (Folstein et al., 1975).

#### Primary outcome measure

2.2.7.

##### Beck’s Depression Inventory (BDI-II)

2.2.7.1.

The scale developed by Beck et al. (1961) was adapted and validated in Portuguese by Martins et al. (Martins et al., 2000; Coelho et al., 2002) aims to differentiate between depressed and non-depressed individuals, as well as to measure the severity of depressive symptomatology. It includes 21 items grouped into three factors: Cognitive Factor (*n* = 8 items); Affective Factor (*n* = 6 items); and Somatic Factor (*n* = 7 items). Symptom severity over the past 2 weeks is ranked on a four-point Likert scale, (e.g., sadness, 0 – I do not feel sad; 3 – I am so sad or unhappy that I cannot take it anymore) (Araújo, 2011). The BDI-II has adequate internal consistency, considered by some authors as “excellent” (Coelho et al., 2002). Scores ≤13 indicate minimal depressive symptomatology; scores between 14 and 19 indicate mild depression; scores between 20 and 28 indicate moderate depression; and scores >28 indicate severe depression (Beck et al., 1966).

#### Secondary outcome measures

2.2.8.

##### Montgomery-Asberg Depression Rating Scale (MADRS)

2.2.8.1.

This instrument is a 10-item rating scale developed by Montgomery and Åsberg (1979). The severity of each symptom is rated from 0 to 6, with higher scores indicating more severe symptoms. Snaith et al. (1986) proposed the following total score interpretations: 0 –6 indicate no symptoms; 7 – 19 indicate mild depression; 20 – 34 indicate moderate depression and 35 and greater indicates severe depression. The reliability of the MADRS ranges from α = 0.64 – 0.89 (Huijbrechts et al., 1999). A methodological study to adapt this instrument to the Portuguese population will be conducted within this study.

